**Methods/Design:**

The I*N*CA trial is a double-blind, placebo-controlled clinical trial with two parallel treatment arms (arm 1: norfloxacin 400 mg once daily; arm 2: placebo once daily; 12-month treatment and observational period). Balanced randomization of 186 eligible patients with stratification for the protein content of the ascites (<15 versus ≥15 g/L) and the study site is planned. In this multicenter national study, patients are recruited in at least 13 centers throughout Germany. The key inclusion criterion is the presence of a *NOD2* risk variant in patients with decompensated liver cirrhosis. The most important exclusion criteria are current SBP or previous history of SBP and any long-term antibiotic prophylaxis. The primary endpoint is overall survival after 12 months of treatment. Secondary objectives are to evaluate whether the frequencies of SBP and other clinically relevant infections necessitating antibiotic treatment, as well as the total duration of unplanned hospitalization due to cirrhosis, differ in both study arms. Recruitment started in February 2014.

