**Figure 1 Fig1:**
[figure not shown]
**Study flowchart.** Overall, 186 patients meeting the inclusion criteria and no exclusion criteria are randomly assigned to two treatment arms. Especially, present SBP has to be ruled out, and patients have to be verified to carry at least one of the three common *NOD2* variants. It is expected that about 1,400 patients need to be evaluated to finally randomize the calculated 186 patients. SBP, Spontaneous bacterial peritonitis.

The patients allocated to arm 1 receive 400-mg norfloxacin capsules (Norfloxacina ABC; ABC International Pharma, Ivrea, Italy) once daily. In arm 2, the patients receive an identically looking capsule containing no active ingredient (placebo) once daily. The treatment and observational periods are 12 months for both groups. Treatment will not differ between arms.

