### Frequency and scope of study visits and interventions

All patients who have already developed ascites should be screened for trial participation. Particularly, SBP has to be excluded, and ascitic protein content has to be determined by a clinically indicated index paracentesis (maximally 10 days prior to baseline visit). Patients who cannot undergo paracentesis because of small amounts of ascites can be included in the trial only if SBP is unlikely, taking into account clinical and blood test indicators. Hereafter potentially eligible patients must be informed about the study and genetic testing by an investigator with the use of a specific information sheet. Informed consent to study participation and genetic testing is mandatory for a further evaluation of patients, and especially *NOD2* genetic testing, using patients’ blood specimens. At the baseline visit (within 28 days before randomization) and during treatment within the trial, only noninvasive or minimally invasive interventions are scheduled (Table 3). Patients who fulfill all inclusion criteria but no exclusion criteria proceed to randomization. Treatment with the study medication must be initiated within 7 days after randomization. Adverse reactions to the study medication are more likely to occur early after treatment initiation, so that closely scheduled visits are implemented for the first 4 weeks. Thereafter, and for the remainder of the trial, the study visits are less frequent (Table 4) and, at predefined time points only, telephone interviews are scheduled to record any (serious) adverse event (AE) as well as primary and secondary endpoint information. Patients are regularly treated within the trial for 12 months. Patients who must definitely stop the study medication for any reason (for example, SBP,prolongation of QTc above 500ms [QTc; QT interval corrected for heart frequency using Bazett’s formula]) will complete the trial without taking the trial medication and attend the regular visits. Patients with SBP during the trial will be unblinded. Patients who undergo liver transplantation or who revoke their consent to participate are censored for the analysis with the date of withdrawal.

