### Statistical analyses

#### Primary statistical aim

The confirmatory part of the statistical analysis is the assessment of treatment efficacy by testing the null hypothesis (H0), “The survival of patients treated with norfloxacin is equal to the survival of patients treated with placebo”, against the alternative hypothesis (H1), “The survival of patients treated with norfloxacin is better than the survival of patients treated with placebo”, by using a one-sided log-rank test with a significance level α = 5%. Antibiotic primary and secondary SBP prophylaxis with norfloxacin showed no negative effects on survival in previous trials and meta-analyses [7,10,12,13,22]. Moreover, there is no evidence for a preponderance of deleterious treatment effects associated with norfloxacin in this patient group, which justifies a one-sided test. All patients who receive at least one dose of norfloxacin or placebo are included in the analysis as an intention-to-treat approach. Incomplete information is accounted for by censoring.

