#### Sample size calculation

To identify a difference of 20% survival rate after 12 months (60% versus 40%, one-sided log-rank test, α = 0.05, 1 − β = 0.8), and to account for a 17% loss due to dropout during treatment, 186 patients carrying *NOD2* variants have to be included in the trial. Sample size calculation is based on the previous observation that patients carrying at least one *NOD2* variant have a deleterious outcome with a survival of only 40% within 12 months, as compared to 73% of patients with wild-type genotypes at all three *NOD2* loci [18], and an increase in survival rate from 48% to 60% after 12 months in a recent randomized controlled trial in which SBP primary prophylaxis was investigated without taking *NOD2* genotypes into account [17]. In studies in which norfloxacin was administered for 12 months or longer to patients with liver cirrhosis and ascites, non-compliance rates ranged from 5% to 8% [17,23]. Although loss to follow-up has been inconsistently reported, the two landmark studies on secondary SBP prophylaxis had rates of up to 9% for loss to follow-up. As a conservative estimate, we calculated our projected sample size with the reported maximum of 17% loss to follow-up and non-compliance. Among all patients considered for the I*N*CA trial, only 25% carry at least one *NOD2* risk allele [18]. Moreover, we expect that 25% of eligible patients to drop out because of lack of informed consent, and a maximum of 10% of the total number of patients with ascites are expected to present with SBP, leading to exclusion. Thus, a total of 1,380 patients with cirrhosis and ascites initially need to be evaluated for the study. Patients evaluated but not included are documented and reported according to the CONSORT statement (http://www.consort-statement.org/).

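### Patients who revoke consent are censored on that day although the endpoint needs only vital status; asking separately for vital-status permission is a cheap improvement

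*Protocol article*

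**What the plan says.** The abstract (Methods/Design) states: "The primary endpoint is overall survival after 12 months of treatment". The text under Figure 1 adds: "The treatment and observational periods are 12 months for both groups".

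The section on frequency and scope of study visits and interventions treats two kinds of departure differently:

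- Patients who have to stop study medication for good "will complete the trial without taking the trial medication and attend the regular visits". Stopping the drug therefore does not end follow-up.
- Patients "who revoke their consent to participate are censored for the analysis with the date of withdrawal". Here follow-up for the primary endpoint ends.

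The same section says that "telephone interviews are scheduled to record any (serious) adverse event (AE) as well as primary and secondary endpoint information". Table 4 lists nine such calls.

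The primary statistical aim adds: "Incomplete information is accounted for by censoring". It describes the analysis set as follows: "All patients who receive at least one dose of norfloxacin or placebo are included in the analysis as an intention-to-treat approach".

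On expected losses, the sample size section says that "we calculated our projected sample size with the reported maximum of 17% loss to follow-up and non-compliance".

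**The concern.** Whether a patient is alive at month 12 can be learned without a visit, a sample or adjudication. The protocol already separates taking the drug from being followed, and it already collects endpoint information by telephone. Yet the rule as stated lets revoked consent to participate also end the count of deaths, with no step in between.

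The log-rank test and the Kaplan-Meier estimate are valid under censoring only if patients who leave have the same later risk of death, within arm, as those who stay. In decompensated cirrhosis that is doubtful: patients who give up on the trial may be sicker. If they are, survival in that arm is overstated. If the excess risk differs between arms, the confirmatory one-sided comparison is distorted, and the assumption cannot be tested for patients whose vital status was not collected.

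**Working it through.** **Inputs from the article.** 186 patients, 1:1, so 93 per arm; 12-month survival 60% versus 40%; one-sided log-rank test, α = 0.05, power 0.80; 17% allowance for loss to follow-up and non-compliance together; cited loss to follow-up up to 9%; cited non-compliance 5% to 8%. The 17% equals 8% + 9%.

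**Assumptions, because the article gives no figure.** Share *d* who revoke consent: 5%, 9% or 17%. Withdrawal times uniform over the 12 months. Exponential survival. Hazard after withdrawal *k* times the hazard before it, *k* = 1, 2 or 3.

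**1. The planned size reproduces.** HR = ln 0.6 / ln 0.4 = 0.557. Freedman: events = (1.645 + 0.842)² × [(1 + 0.557)/(1 − 0.557)]² ≈ 77. With a mean death probability of 0.5, 77/0.5 = 154 patients; 154/0.83 = 186.

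**2. Patients who leave alive, and deaths lost.** Let λ = −ln S per 12 months.

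- Share leaving alive = d(1 − S)/λ. The factor (1 − S)/λ is 0.783 for S = 0.6 and 0.655 for S = 0.4, sum 1.438. So 93 × 0.09 × 1.438 ≈ 12 patients at 9%, and 93 × 0.17 × 1.438 ≈ 23 at 17%.
- Deaths lost with unchanged hazard: 93 × d × [(0.783 − 0.6) + (0.655 − 0.4)] = 93 × d × 0.438. This gives 2.0, 3.7 and 6.9 deaths at 5%, 9% and 17%.
- Deaths lost at *k* = 3: about 7 at 9% and 14 at 17%.

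**3. Power.** Full ascertainment gives 93 expected deaths and 88.0% power (Schoenfeld). With unchanged later hazard, 91.0, 89.3 and 86.1 deaths remain, with power 87.3%, 86.8% and 85.7%. All exceed the 77 events needed. Power is not the issue.

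**4. Bias in each arm's survival.** Kaplan-Meier with these patients censored still estimates S. True survival is (1 − d)S + d(S − S^k)/[(k − 1)λ] for k > 1. Example, d = 0.09, k = 2, S = 0.6: 0.91 × 0.6 + 0.09 × (0.6 − 0.36)/0.511 = 0.546 + 0.042 = 0.588.

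| Withdrawal | Later hazard | True survival, norfloxacin (estimated 60%) | True survival, placebo (estimated 40%) |
|---|---|---|---|
| any | ×1 | 60.0% | 40.0% |
| 5% | ×2 | 59.3% | 39.3% |
| 5% | ×3 | 58.9% | 38.9% |
| 9% | ×2 | 58.8% | 38.8% |
| 9% | ×3 | 58.0% | 38.1% |
| 17% | ×2 | 57.8% | 37.7% |
| 17% | ×3 | 56.2% | 36.3% |

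**5. Bias in the difference (estimated as 20 points).** If the later hazard rises in both arms alike, the true difference stays near 20 points in every row. If it rises in the norfloxacin arm only, the true difference is 18.8 points (9%, ×2), 17.8 (17%, ×2) or 16.2 (17%, ×3). If it rises in the placebo arm only, it is 21.2, 22.3 or 23.7.

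**6. False-positive rate.** Simulated one-sided 5% log-rank test, 93 per arm, true 12-month survival 40% in both arms, later hazard raised in the norfloxacin arm only, 20,000 trials per setting. Rejection rate at 9% withdrawal: about 7% (×2) and 8.5% (×3). At 17%: about 9% and 13%. With vital status kept for everyone it is about 5% to 6%.

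**The case against.** The strongest case for the rule is that it is conventional. Once consent to participate is revoked, new data generally need further permission, and censoring on that date is the usual handling. This stands, and the fix keeps it for anyone who refuses vital-status follow-up as well.

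Three stronger readings are tempting, and the article does not support them.

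- *That stopping the capsules loses patients from the primary analysis.* It does not; those patients stay in the trial off drug and keep attending visits.
- *That the trial has no vital-status option at all.* A condensed article cannot show this. Consent and withdrawal forms and sensitivity analyses commonly sit in documents not shown here. What the article does state is one unqualified analysis rule, and that is what is questioned.
- *That survival is overstated wherever more patients withdraw.* More withdrawals with the same later risk do not bias Kaplan-Meier. Bias needs a different later hazard, and material distortion of the contrast needs that hazard to act differently in the two arms. With indistinguishable capsules, a strong difference between arms is possible but not shown.

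The rates are also borrowed. The 9% is loss to follow-up in two secondary-prophylaxis studies, not consent revocation. The 17% includes non-compliers, who remain under follow-up. The 2- to 3-fold hazard is assumed.

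The 17% allowance does not answer the concern, however. It adds patients and so protects power; it cannot remove bias.

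**Conclusion.** The point holds as a cheap improvement, not as an error or a contradiction. The stated rule discards deaths after consent is revoked, although the endpoint could still be learned for any patient who permits it.

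The likely effect is small: about 1 to 2 points of overstated 12-month survival in the affected arm at 5% to 9% withdrawal with doubled or tripled later hazard, and 2 to 4 points at the 17% upper bound. It is zero if the later hazard is unchanged, and the treatment difference is nearly untouched if the increase is the same in both arms. The case that matters is informative withdrawal concentrated in the norfloxacin arm, where the one-sided error rate could rise from 5% to somewhere between 7% and 13% under the assumptions above. Nothing in the article shows that this will happen; the rule simply leaves the trial unable to exclude it.

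The same sentence also censors at liver transplantation. That is a separate question and is not judged here.

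**What to change.** Change the censoring rule for revoked consent along these lines:

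- A patient who revokes consent to participate is asked separately for permission to ascertain vital status at month 12, by telephone, from the treating physician or from records.
- If permission is given, the patient stays in the primary analysis and a death up to month 12 counts.
- Only a patient who refuses this as well is censored at the withdrawal date.
- The number censored in this way is reported by arm, with a sensitivity analysis for informative censoring. Options are to vary the later hazard by arm, or to count these patients as dead at or soon after censoring.

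If the full protocol or the consent documents already contain such an option, it is enough to align the censoring rule with it.

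The cost is one line in the consent or withdrawal form, an ethics notification, and a vital-status query per withdrawn patient: about 12 at 9% withdrawal and 23 at the 17% upper bound. Some patients will still refuse. The change should be made while patients are still in the trial, because permission is harder to obtain once they have left.

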**Table 3 Tab3:** **Study-specific actions**
^**a**^

**Action**	**Baseline period**	**Study visits**	**Telephone visits**
Informed consent	X		
Checking inclusion and exclusion criteria	X		
Demographics	X		
Medical history (with focus on liver disease)	X		
*NOD2* genetic testing	X		
Concomitant diseases	X	X	X
Concomitant medications	X	X	X
MELD and Child-Pugh-scores	X	X	
Clinical assessment and vital signs	X	X	
12-lead ECG	X	X	
Blood tests (safety parameters)	X	X	
Recording of adverse events		X	X
Distribution and return of study medication		X	
Collection of ascites samples (clinically indicated puncture)	X	X	
Collection of stool samples		X	

^a^ECG, Electrocardiography; MELD, Model For End-Stage Liver Disease.

**Table 4 Tab4:** **Visits and time points**

**Baseline period**	**Within 28 days before randomization**
Visit 1	Day 0 (up to 7 days after randomization)
Visit 2	Day 7 (±2 days)
Telephone visits 1 to 9	Weeks 4, 8, 16, 20, 28, 32, 40, 44 and 48 (±7 days)
Visits 3 to 5	Weeks 12, 24 and 36 (±7 days)
Visit 6	Week 52 (±7 days) or shortly after close-out

Patients are allowed any additional, necessary treatment, which is at the discretion of the physician in charge. However, to avoid treatment bias, any long-term treatment with antibiotics is prohibited, whereas temporary antibiotics for treatment of acute infections are permitted. Study medication can be paused for a maximum of 7 days.

In case of AEs, the investigators at each trial center judge the severity and causality of the AE and decide on an individual basis to continue, pause or terminate the study drug. The compliance of study participants is determined by the ratio of pills actually taken (pills delivered minus pills returned) and pills expected to be taken.

Because treatment with fluoroquinolones rarely causes QT interval prolongation, electrocardiography (ECG) with determination of the QTc is mandatory for safety reasons at baseline, to visit 1 before first intake of study medication as well as to study visits 2 through 6 during trial participation. The actions to be taken in case of marked prolongation of the QTc (ECG controls, modification of concomitant medication, pausing or termination of the study drug) are in line with published guidelines and recommendations [20,21].

At the baseline visit, an ascites sample derived from the index paracentesis is collected and stored. In case of recurrent ascites and suspicion of SBP, a diagnostic paracentesis must be performed (according to standard of care) to diagnose or exclude SBP. In this case, ascites samples are collected. Moreover, stool samples are collected regularly throughout the study (visits 1 through 6) for additional analyses to evaluate the effects of long-term treatment with antibiotics on intestinal microbiome composition (sequence-based analyses investigating absolute and relative abundance as well as diversity of microorganisms; sequence- and culture-based resistance analyses).

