## Background

Cirrhosis is the final common pathway of chronic liver diseases [1]. The alcoholic and non-alcoholic fatty liver diseases, as well as chronic viral hepatitis, are the most important causes of cirrhosis. The increasing liver disease rates, with more than 800,000 annual deaths worldwide due to complications of cirrhosis [2], demonstrate the high socioeconomic impact of liver diseases and the need for improved patient care and disease management.

Patients with cirrhosis are approximately ten times more likely to develop bacterial infections than healthy persons [3]. Spontaneous bacterial peritonitis (SBP) and urinary tract infections are observed most frequently [4]. The occurrence of bacterial infections is also highly relevant for the patients’ prognosis, with the overall median mortality of infected patients with cirrhosis quadrupling to more than 60% at 12 months [3]. The prevalence of SBP is 10% in hospitalized patients and 1.5% to 3.5% in outpatients with cirrhosis [5,6]. Although antibiotic therapy reduces the acute mortality of hospital inpatients with SBP, there is a very high probability of recurrence and death (up to 70%) within 1 year after an episode of SBP [7-9].

Long-term antibiotic prophylaxis has been shown in randomized controlled trials to significantly reduce the risk of SBP recurrence [7], and it is thus advised for all patients who have survived an index SBP [10]. The best data exist for fluoroquinolones, especially for norfloxacin [7,11]. Primary prevention of SBP with antibiotics to avoid a first episode is currently not uniformly recommended for patients with ascites, because the existing data are conflicting and the intervention might promote the development of multidrug-resistant bacteria [12-16]. Thus, long-term antibiotic prophylaxis should be administered only to subgroups with the highest risk [10]. In one randomized controlled trial, Fernández and co-workers showed that primary prophylaxis with norfloxacin in a clinically defined high-risk population (protein level of the ascites below 15 g/L and advanced liver failure or impaired renal function) significantly reduced the risk for a first episode of SBP and short-time survival [17].

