## Methods/Design

### Trial design and ethical considerations

The trial has been designed to assess the effect of antibiotic primary prophylaxis on survival in carriers of *NOD2* risk variants without SBP. Figure 1 summarizes the design of the study. The I*N*CA trial is a double-blind, placebo-controlled clinical trial with two parallel treatment arms. It is planned to randomly allocate 186 eligible patients to one of these arms (1:1 ratio). Balanced randomization, stratified for the protein content of the ascites (<15 g/L or ≥15 g/L, given that a low protein content is an established risk factor for SBP) and the study center, will be performed as centralized, computer-based block randomization using separate randomization lists for each stratum. Only the central and independent pharmacy (Heidelberg University Hospital) performing the randomization procedure, and neither the investigators nor the patients, will be aware of the allocation sequence or the block size used. Blinding of participants and study personnel responsible for treatment and outcome assessment is ensured by identical encapsulation of placebo and active substance that makes both indistinguishable, as well as by the use of identical blisters and folding boxes. The unique patient randomization number labeled on the boxes makes the medication patient-specific. The confidential block size ensures randomization concealment after emergency un-blinding because of safety reasons or after unblinding due to SBP. Access to emergency envelopes is regulated at all sites.

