### Participants

In general, all patients with liver cirrhosis and ascites should be screened for the I*N*CA trial. Importantly, only patients verified to carry at least one of the three common *NOD2* risk variants (p.R702W, p.G908R or c3020insC) can ultimately participate in the trial. The most important exclusion criteria are a present SBP or a previous history of such, as well as long-term antibiotic treatment, irrespective of the indication. Table 1 provides a list of the inclusion and exclusion criteria. In this multicenter national study, patients will be recruited at a minimum of 13 participating referral centers. These centers have specific clinical expertise in treating patients with advanced liver diseases, and ten of them are centers for liver transplantation. These centers were also selected because of their experience in conducting randomized, controlled trials, their specialized outpatient structure and their collaboration with local primary and secondary care hospitals. The estimated recruitment period is 24 months, and recruitment started in February 2014.

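### The ban on long-term antibiotics has no exception for SBP, so as printed it denies SBP survivors the secondary prophylaxis the article says they should receive

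*Protocol article*

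**What the plan says.** Four statements in the protocol article bear on this.

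- **Concomitant treatment (text after Table 4).** Necessary treatment is left to the treating physician, but with a limit: "to avoid treatment bias, any long-term treatment with antibiotics is prohibited, whereas temporary antibiotics for treatment of acute infections are permitted".
- **Stopping study drug (Frequency and scope of study visits and interventions).** Patients who must stop for good, with SBP and "prolongation of QTc above 500ms" as the examples, "will complete the trial without taking the trial medication and attend the regular visits". For SBP specifically: "Patients with SBP during the trial will be unblinded".
- **Care after SBP (Background).** Of long-term antibiotic prophylaxis the article says "it is thus advised for all patients who have survived an index SBP". On prognosis it says "there is a very high probability of recurrence and death (up to 70%) within 1 year after an episode of SBP".
- **Eligibility (Table 1).** A previous SBP is an exclusion criterion, so an SBP during the trial is in principle the patient's index episode.

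**The concern.** The ban is categorical and names a single exception, short-term treatment of acute infection. That covers the SBP episode itself but not the prophylaxis that follows it. A patient who survives an on-trial SBP stays in the trial, is off study drug, and may not be given a long-term antibiotic. The article's own account of standard care says such a patient should receive one.

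Patient safety is at stake first: these are very high-risk patients, and the primary endpoint is death. Consistency comes second. With at least 13 centres, some could follow the written ban and others usual care, so post-SBP management could vary by site. The stated purpose of the ban, avoiding treatment bias, is a weak reason to withhold advised care from someone already unblinded and permanently off study drug.

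**Working it through.** **1. The chain of rules.**

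| Step | Source | Consequence for a patient with on-trial SBP |
|---|---|---|
| Study drug stopped, patient unblinded, visits continue | Frequency and scope of study visits and interventions | No study norfloxacin, but still under trial rules to month 12 |
| Long-term antibiotics prohibited, short-term treatment excepted | Text after Table 4 | The episode may be treated; prophylaxis afterwards may not be given |
| Long-term prophylaxis advised for every index-SBP survivor | Background | The prohibited treatment is the advised one |
| Previous SBP excluded | Table 1 | The on-trial episode is the index episode |

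**2. Can *treatment* be read as not covering *prophylaxis*?** No. The Participants section describes the exclusion as "long-term antibiotic treatment, irrespective of the indication", while Table 1 calls the same criterion long-term prophylaxis and then, in its next sentence, long-term treatment. The text after Table 4 also uses long-term treatment with antibiotics for what the stool samples are meant to study, and the long-term antibiotic under study is prophylactic norfloxacin. The article uses the two words interchangeably.

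**3. Does physician discretion cover it?** No. The ban is worded as a limit on that discretion. Nothing restricts it to patients still taking study drug.

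**4. Time and contacts left, from Table 4.** Weeks left = 52 − week of SBP. Contacts left = later telephone visits + later clinic visits.

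| SBP at | Weeks left | Telephone visits left (weeks) | Clinic visits left (weeks) | Contacts left |
|---|---|---|---|---|
| Week 12 | 52 − 12 = 40 | 16, 20, 28, 32, 40, 44, 48 (7) | 24, 36, 52 (3) | 10 |
| Week 24 | 52 − 24 = 28 | 28, 32, 40, 44, 48 (5) | 36, 52 (2) | 7 |
| Week 36 | 52 − 36 = 16 | 40, 44, 48 (3) | 52 (1) | 4 |

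Table 3 has concomitant medication recorded at every one of these contacts.

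**5. Sample size, for completeness.** From 60% versus 40% survival, HR = ln 0.6 / ln 0.4 = 0.557. Freedman's formula (one-sided α = 0.05, power 0.8) gives 77 events. With a mean event probability of 0.5, 77 / 0.5 = 154 patients, and 154 / (1 − 0.17) = 185.5, rounded up to 186. The planned figure is reproduced, and none of its inputs concerns care after SBP.

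**6. What might the exception cost in power?** The article gives no inputs for this, so what follows is an illustration on assumed values. Assume that 10% to 30% of placebo patients develop SBP, that the norfloxacin arm has one quarter of that, and that secondary prophylaxis lowers 12-month mortality among SBP patients by 10 to 20 percentage points. Treat the planned 40% and 60% as survival without secondary prophylaxis. With 154 evaluable patients and Schoenfeld's formula (one-sided 0.05), power before any dilution is 82%.

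- 10% SBP, 10 points: placebo survival 0.40 + 0.10 × 0.10 = 0.41; norfloxacin 0.60 + 0.025 × 0.10 = 0.6025; HR 0.568; power 79%.
- 30% SBP, 20 points: placebo survival 0.40 + 0.30 × 0.20 = 0.46; norfloxacin 0.60 + 0.075 × 0.20 = 0.615; HR 0.626; power 63%.

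If the 40% control survival already reflects usual care with secondary prophylaxis, there is no loss.

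**The case against.** The strongest reply is that nobody meant this. Unblinding is prescribed for SBP but not stated for QTc prolongation, and the randomisation section treats it as an event separate from emergency unblinding, speaking of concealment "after emergency un-blinding because of safety reasons or after unblinding due to SBP". Routine unblinding at SBP makes most sense if it guides further antibiotic care. Table 1 lets the absence of secondary prophylaxis stand in for the absence of a previous SBP, which works only if survivors normally receive it. The ban's declared purpose is to protect the blinded comparison, which an unblinded patient off study drug has already left. The trial has ethics and regulatory approval. The article is also a condensed account, and the full protocol may spell out post-SBP care.

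Most of this stands as evidence of intent, and it means the text does not show that any patient was actually refused prophylaxis. It does not change what is written. This is not a detail left out for brevity: the article states a rule covering any long-term antibiotic and lists its exception, which does not reach this case. If the intent contradicts the rule, the rule needs correcting.

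Two further points are fair. The Discussion's ethical defence of placebo, which concerns patients without SBP, adds little, because study drug has been stopped by then; the conclusion does not depend on it. And the week counts in the working show how long the ban would last, not how much harm it would do.

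**Conclusion.** The concern holds for the printed text and should be fixed. Followed literally, the rule withholds from SBP survivors the care that the article itself says is advised for all of them, for up to 40 weeks after an SBP at week 12 and longer after an earlier one. The number of patients affected and the outcomes attributable to withheld prophylaxis cannot be estimated: the article gives neither a 12-month SBP incidence nor survival of the acute episode in this population.

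Confidence is medium. The conclusion assumes that the full protocol contains no exception, or that sites work from the rule as published. The sample size, primary test and analysis set are unaffected.

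**What to change.** Add one exception after the ban, for example:

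> *After study medication has been permanently stopped and the patient unblinded because of SBP, guideline secondary prophylaxis is permitted and is recorded as concomitant medication.*

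Keep the ban for all other patients, including those who stop study drug for other reasons such as QTc prolongation, so that open-label primary prophylaxis stays prohibited. Keep SBP patients in the primary analysis as randomised, without censoring at SBP. Report by arm how many start long-term antibiotics after SBP.

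The cost is one sentence. No new data collection is needed, since concomitant medication is already recorded at every contact. The trade-off should be acknowledged: the comparison becomes primary prophylaxis against prophylaxis only after a first SBP, which may shrink the survival difference by an amount the article does not allow one to estimate. That is an acceptable price for giving these patients advised care.
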